## Abstract

**Background:**

Abdominal and thoracic aortic aneurysms (A/TAA) are an important cause of mortality amongst the older population. Although A/TAA repair can be performed with low peri-operative risk, overall life expectancy remains poor in the years that follow surgery. The majority of deaths are caused by heart attack or stroke, which can both be prevented by cardiac rehabilitation (CR) in patients with clinically-manifest coronary artery disease. A Cochrane review has urged researchers to widen the use of CR to other populations with severe cardiovascular risk, and patients surviving A/TAA repair appear ideal candidates. However, it is unknown whether CR is feasible or acceptable to A/TAA patients, who are a decade older than those currently enrolling in CR. Aneurysm-CaRe is a feasibility randomised controlled trial (RCT) that will address these issues.

**Methods and design:**

Aneurysm-CaRe is a pilot RCT of CR versus standard care after A/TAA repair, with the primary objectives of estimating enrolment to a trial of CR after A/TAA repair and estimating compliance with CR amongst patients with A/TAA. Aneurysm-CaRe will randomise 84 patients at two sites. Patients discharged from hospital after elective A/TAA repair will be randomised to standard care or enrolment in their local CR programme with a protocolised approach to medical cardiovascular risk reduction. The primary outcome measures are enrolment in the RCT and compliance with CR. Secondary outcomes will include phenotypic markers of cardiovascular risk and smoking cessation, alongside disease-specific and generic quality-of-life measures.

**Trial registration:**

ISRCTN 65746249 5 June 2014

## Background

Abdominal and thoracic aortic aneurysms (A/TAAs) are a significant health problem that account for approximately 4 deaths per 100,000 population per year [1]. A/TAA repair can be performed with low peri-operative risk [2] and is an effective means of mitigating the long-term risk of mortality caused by A/TAA rupture. However, overall life expectancy remains poor in the years that follow surgery because patients with A/TAA have widespread atherosclerosis and considerable cardiovascular risk factors, which cause an unusually high rate of heart attacks, strokes and major amputation [3] compared with the wider population [4,5].

Patients with A/TAA have similar cardiovascular risk factors to those with clinically-manifest coronary artery disease (CAD) and might benefit from the application of similar therapeutic strategies for secondary prevention. High-quality evidence has demonstrated that cardiac rehabilitation (CR) improves outcomes after cardiac surgery or myocardial infarction, improving adherence to evidence-based care and both the quality and quantity of life [6]. CR is a complex intervention delivered typically over 8–12 weeks, which combines supervised exercise, dietary and lifestyle modification, smoking cessation, and optimal medical therapy for cardiovascular risk factors. This programme is very cost-effective: CR is the third most economic intervention for reducing cardiovascular mortality, after aspirin and beta-blockers [7]. Extensive national infrastructure is in place for delivering this service, and a Cochrane review has urged researchers to apply CR in other populations with severe cardiovascular disease [6].

Patients undergoing A/TAA repair appear ideal candidates for postoperative CR and are at even greater risk of cardiovascular mortality than patients undergoing cardiac surgery: just 65% remain alive at 5 years after aneurysm repair [8] compared with 90% at 5 years after cardiac surgery [9]. The definitive impact of CR on survival after A/TAA repair could be studied by a multicentre randomised trial of CR after A/TAA repair. This would require 1140 patients to demonstrate an absolute improvement of 9% in 3-year survival, with 90% power, a calculation aiming to bridge the gap in survival between A/TAA patients and age-/gender-matched controls without A/TAA [4]. However, prior to such a considerable undertaking, data are required to estimate the feasibility and efficacy of CR in A/TAA patients.

Aneurysm-CaRe is a pilot randomised controlled trial of CR after A/TAA repair that will address these issues. Patients undergoing A/TAA repair are typically 10 years older than those currently recruited to CR [4,6] and it is therefore not known whether CR would be feasible or acceptable in this group. It also remains unknown whether an intensive programme of CR can improve phenotypic markers of cardiovascular risk after A/TAA repair. The life expectancy of patients with A/TAA may not be modifiable by CR and the equipoise justifies a trial such as Aneurysm-CaRe. Cigarette smoking is strongly associated with the development of A/TAA and is the most important modifiable risk factor for patients with vascular disease [10]. The period after A/TAA surgery presents a unique window for preventing a return to smoking [11] and enrolment in a CR programme provides a novel opportunity for quantifying the effects of exercise on smoking cessation in patients with A/TAA [12]. Standard care may provide as few as 40% of A/TAA patients with appropriate cardiovascular risk management (using antiplatelet agents, statins, angiotensin-converting enzyme inhibitors or beta-blockers) [13] and it is likely that attainment of risk-factor targets is even lower than in comparable CAD populations. These data highlight an unmet clinical need. Aneurysm-CaRe presents an important opportunity to improve life expectancy in a high-risk population (A/TAA patients) using an existing national service (CR) and the accompanying infrastructure.

## Methods

### Trial design and objectives

Aneurysm-CaRe is a pilot randomised controlled trial comparing CR with standard care after elective A/TAA repair. It is envisaged that this study will inform Aneurysm-CaRe II: a large-scale definitive phase III randomised controlled trial of CR after elective A/TAA repair.

The objectives of Aneurysm-CaRe are to quantify the proportion of patients surviving A/TAA repair that agree to enrol in a RCT of CR and to quantify compliance with CR in terms of attendance amongst those randomised to CR. The secondary objectives of Aneurysm-CaRe are to quantify the effect of CR compared with standard care on phenotypic markers of cardiovascular risk, patient behaviour/biometrics and quality of life. Finally, Aneurysm-CaRe aims to enable optimisation of the patient pathway for a definitive RCT and identification of pitfalls such as exposure bias or methodological heterogeneity.

### Ethical approval

Full ethical approval has been gained from the NRES Committee London (Bloomsbury), reference 13/LO/0395.

### Randomisation

Patients discharged from hospital after elective endovascular or open thoracic or abdominal aortic aneurysm repair will be randomised, in a 1:1 ratio, between the intervention arm (“Cardiac Rehabilitation – CR”) and the control arm (“Standard Care”) (Figure 1). Secure Internet-based central randomisation will be provided by an NIHR-accredited clinical trials unit. A minimisation algorithm will be utilised to ensure stratification variables (age, gender and study site) are balanced between groups. Each site and randomiser will be provided with a unique login and password to allow access to the randomisation service.

**Figure 1 Fig1:**
[figure not shown]
CONSORT 2010 flow diagram for pilot randomised controlled trial of cardiac rehabilitation vs. standard care after aortic aneurysm repair (Aneurysm-CaRe).

### Inclusion criteria

All patients who are discharged home alive after undergoing elective thoracic or abdominal aortic aneurysm repair at St George’s Vascular Institute or Leicester Royal Infirmary during the recruitment period will be eligible for participation and offered the chance to enrol.

### Exclusion criteria

The exclusion criteria are:Any patient under the age of 50 years, or with aortic pathology secondary to connective tissue disease (including Marfan’s and Loeys-Dietz syndromes)Anyone unable or unwilling to consent to participationAnyone unable or unwilling to attend CR sessionsAny patient deemed too unfit for the CR programme by the Lead CR nursePatients undergoing expedited or emergent surgical intervention for symptomatic or ruptured aortic aneurysms

A pseudonymised registry will be kept to record the proportion of patients undergoing elective aneurysm repair but meeting exclusion criteria for Aneurysm-CaRe during the study period.

### Primary outcome measures

Enrolment: the proportion of patients surviving A/TAA repair and meeting Aneurysm CaRe inclusion criteria, that agree to enrolment in the feasibility RCT.Compliance with CR therapy in the group randomised to CR (defined as the proportion of patients demonstrating attendance at 100% of scheduled CR sessions over 8–12 weeks; the period of CR offered is dependent on individual patient needs).

### Secondary outcome measures

Time to death.Time to first adverse cardiovascular event after aneurysm repair.The composite “adverse cardiovascular event” outcome includes: non-fatal myocardial infarction, stroke, non-traumatic amputation and revascularisation. The revascularisation endpoint comprises strictly defined coronary procedures (coronary artery bypass graft surgery, percutaneous coronary interventions and percutaneous coronary interventions) and peripheral vascular procedures (embolectomy, bypass and angioplasty). In the absence of relevant COMET outcomes (www.comet-initiative.org), this outcome measure mirrors the composite cardiovascular endpoint measured for previous randomised RCTs of cardiovascular risk reduction [14]. Analysis of the “composite cardiovascular disease event” endpoint will be adjusted to account for “competing risks”, for example, the intervention reducing the risk of one event but increasing the risk of another [15]. Outcomes will be compared with the BHF-funded National Audit of CR for attendance, adherence, and outcomes with MI, PCI and CABG patients.Intermediate phenotypic markers of cardiovascular risk measured at enrolment, 12-weeks after randomisation to CR and 6-months after randomisation to CR or standard care: serum lipids (total cholesterol, HDL and LDL), systolic and diastolic blood pressure, HbA1C, BNP, troponin, hsCRP, fibrinogen, homocysteine, urate, eGFR, serum insulin levels and echocardiographic measures of cardiac function. We will also be testing for urinary microalbuminuria at each time point.Indicators of patient behaviour and lifestyle, and patient biometrics, including: waist:hip ratio, waist circumference, BMI, ankle-brachial pressure index (ABPI) and toe pressures. Smoking cessation outcomes will include: salivary cotinine, expiratory carbon monoxide (<10 ppm), “prolonged abstinence” [16] and attendance at NHS stop-smoking services. Physical activity levels will be assessed by a 7-day-recall interview [17].Changes in patients’ attitudes to cardiovascular risk and their knowledge of their condition.Quality of life: EQ5D5L questionnaires will be administered at baseline, enrolment, 12-weeks after randomisation to CR or standard care and 6 months after randomisation to CR or standard care.Cost-effectiveness: Mean costs and quality adjusted life years will be compared on an intention-to-treat basis. The perspective will be the NHS and PSS. The analysis will include hospital re-admissions and pharmaceuticals. Unit cost will be obtained from the published literature.

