### Informed consent

Patients will be identified and given information about the trial from three settings and seen by the local Principal Investigator, a Research Investigator or the Lead CR Nurse:At the surgical outpatient clinic when it is certain that aortic aneurysm repair will be scheduled. The trial will be discussed with the patient and the patient given a Patient Information Sheet.At the pre-operative assessment clinic.On admission for surgery, prior to aortic aneurysm repair.

Formal written consent will be obtained after the patient has undergone aortic aneurysm repair and been deemed fit for discharge from hospital.

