### Randomisation

After informed consent has been obtained, a nominated research investigator will randomise the patient using a secure online NIHR-accredited Clinical Trials Unit Randomisation Service (King’s Clinical Trials Unit). The patient will be allocated a unique trial identification PIN number. Neither investigators nor patients will be blinded to treatment allocation. The patient’s GP will be notified of the treatment allocation, and supplied with a reminder letter highlighting current NICE guidelines for the medical management of cardiovascular risk in patients with peripheral vascular disease.

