### Treatment and follow-up

Patients randomised to CR will be seen by a member of the Cardiac Rehabilitation team on the ward prior to discharge if possible, or at the induction CR meeting scheduled 4–6 weeks after aortic aneurysm repair. The CR Arm will receive a protocolised approach to intensive medical risk factor reduction (Figure 3) in addition to enrolment in the local multimodal Cardiac Rehabilitation programme, which should follow national guidelines (www.cardiacrehabilitation.org.uk). CR is an existing national service, comprising a protocolised 8–12 week regime of supervised exercise, lifestyle modification, dietary interventions, psychological assessment and medical risk modification. Each weekly session takes 1 to 2 h and is supervised by two nurses trained in CR, two qualified physiotherapists and one occupational therapy technician. Patients assessed as being low-risk attend sessions with a maximum of 20 patients; those deemed high-risk attend sessions with 12 patients. Each session begins with a “check-in” consisting of a blood pressure and heart rate check and a review of each patient’s progress to date. The group then proceed through a supervised warm-up of 10–15 min, followed by the main exercise session of 45 min. This is followed by a warm-down, and finally a “check-out” consisting of further blood pressure and heart rate measurement.

An individual assessment is made of each patient’s progress and needs; in some cases this involves extending the duration of the patient’s participation in the programme beyond the initial 8 weeks. The patients that have been randomised to “treatment as usual” will receive “standard” follow-up, i.e. routine post-operative out-patient appointments and/or follow-up scans as necessary and GP-based management of their co-existing co-morbidities such as hypertension. Local standards for routine outpatient care after A/TAA repair will be unaffected by the trial, including existing appointments for endograft surveillance and vascular surgery outpatient review.

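### Time to first cardiovascular event runs from aneurysm repair, but patients are randomised only once fit for discharge, so in-hospital events before randomisation count as outcomes

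*Protocol article*

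**What the plan says.** Under Secondary outcome measures, the article gives two time-to-event outcomes. Time to death has no stated starting point. The other is "Time to first adverse cardiovascular event after aneurysm repair", where the event is a composite of "non-fatal myocardial infarction, stroke, non-traumatic amputation and revascularisation". The revascularisation element takes in coronary procedures and also peripheral ones, embolectomy among them. There is no exception for events during the operative admission.

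The order of surgery and allocation is set elsewhere. Informed consent states: "Formal written consent will be obtained after the patient has undergone aortic aneurysm repair and been deemed fit for discharge from hospital". The Randomisation section that follows it continues: "After informed consent has been obtained, a nominated research investigator will randomise the patient". The first Randomisation section is consistent with this: "Patients discharged from hospital after elective endovascular or open thoracic or abdominal aortic aneurysm repair will be randomised, in a 1:1 ratio".

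On who enters, Inclusion criteria admit "All patients who are discharged home alive after undergoing elective thoracic or abdominal aortic aneurysm repair" at the two sites. Exclusion criteria do not mention a non-fatal peri-operative event. The nearest filter is the Lead CR nurse's judgement that a patient is too unfit for the programme.

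**The concern.** A comparison of randomised arms should count events from the point of allocation. Here the outcome window opens at surgery, and the whole in-hospital recovery falls inside it before any patient is allocated. Two things follow from the wording.

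- Events that CR could not have influenced enter the numerator of both arms.
- Because only the first event counts, a patient with an in-hospital event can contribute nothing afterwards, although the period afterwards is the only one that carries information about CR.

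At stake is how the trial's one composite clinical-event outcome can be interpreted. A rate that includes operative complications is not a post-discharge event rate, and a risk ratio computed on it is pulled towards 1. The same section also plans to compare outcomes with the national CR audit. The planned adjustment for competing risks concerns trade-offs between types of event and does not move the time origin.

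**Working it through.** **Setting the sections side by side.**

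1. Start of the outcome window: aneurysm repair (Secondary outcome measures).
2. Consent: after repair, when fit for discharge (Informed consent).
3. Randomisation: after consent (second Randomisation section).
4. Eligibility: alive and discharged home, with no exclusion for a non-fatal in-hospital event (Inclusion and Exclusion criteria).
5. Any rule limiting the composite to events after randomisation: none found.

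Steps 1 to 3 put the interval from surgery to randomisation inside the window. Steps 4 and 5 mean that a patient with an event in that interval can be randomised with the event counted.

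**How many patients.** The article gives no peri-operative event rate, so there is no stated figure to reproduce. With q the assumed share of randomised patients who had a qualifying event before randomisation, the expected number is 84 × q:

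- q = 2%: 84 × 0.02 = 1.7
- q = 5%: 84 × 0.05 = 4.2
- q = 8%: 84 × 0.08 = 6.7

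**What this does to a treatment effect (illustration on assumed rates).** Let c be the 6-month control risk after randomisation, set to 5% or 10%. Let t = 1 − (1 − c)^0.70 be the CR risk under an assumed hazard ratio of 0.70. This gives t = 3.53% or 7.11%. With q equal in expectation in both arms, counting from surgery gives

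- control risk C = q + (1 − q)c
- CR risk T = q + (1 − q)t

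| q | c | C | T | Risk ratio from surgery, T/C | Risk ratio from randomisation, t/c | Share of control first events before randomisation, q/C |
|---|---|---|---|---|---|---|
| 2% | 5% | 6.90% | 5.46% | 0.791 | 0.705 | 29% |
| 5% | 5% | 9.75% | 8.35% | 0.856 | 0.705 | 51% |
| 8% | 5% | 12.60% | 11.24% | 0.892 | 0.705 | 63% |
| 2% | 10% | 11.80% | 8.97% | 0.760 | 0.711 | 17% |
| 5% | 10% | 14.50% | 11.75% | 0.811 | 0.711 | 34% |
| 8% | 10% | 17.20% | 14.54% | 0.845 | 0.711 | 47% |

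The absolute difference is (1 − q)(c − t), so it shrinks only by the factor 1 − q, that is by 2% to 8%. Most of the damage is to the relative effect and to the event rate.

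**How many later events are hidden.** If patients with an in-hospital event had the same later risk as everyone else, the expected number of masked events is 84 × q × (c + t)/2. This runs from 1.68 × 0.0426 = 0.07 (q = 2%, c = 5%) to 6.72 × 0.0855 = 0.57 (q = 8%, c = 10%). Under that assumption, masking costs less than one event in the pilot, and the added events are the larger problem. A higher later risk in these patients would raise the figure.

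**The case against.** The best defence is that the phrase is only a label. Every participant has had a repair, so it may name the clinical setting and not an analysis time zero, and a full protocol or analysis plan could set the origin. That lowers certainty about intent. It does not change what the article says: the same section times the phenotypic markers and quality-of-life questionnaires from randomisation, so that anchor was used elsewhere and not here.

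A second defence is that few such patients will be randomised. Entry requires discharge home, consent, ability to attend CR and being judged fit by the Lead CR nurse, which should remove some patients with an in-hospital stroke, infarction or amputation. This stands, and it is why the 2-8% range may be too high.

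Several stronger readings are tempting but unsupported.

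- *Bias between arms.* Events before randomisation cannot depend on allocation. A chance imbalance is possible with about 42 per arm, but a systematic one is not.
- *A wrong planning figure for the definitive trial.* Background sizes that trial on 3-year survival, not on this composite, and the article does not say the composite rate will be used for planning.
- *Guaranteed event-free time before randomisation.* This is true of death only. For the composite the problem is the reverse, and time to death has no stated origin to criticise.
- *A comparison with expected deaths.* The 65% 5-year survival in Background gives, at a constant hazard, −ln(0.65)/5 = 0.0862 per year, a 6-month risk of 4.2% and 84 × 0.042 = 3.5 deaths. Death is not a listed component of the composite, and that survival is counted from repair, so the figure is no yardstick for post-randomisation composite events.

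**Conclusion.** The point holds on the plain wording. The outcome is counted from surgery, allocation comes later, and nothing excludes events in between. Non-fatal in-hospital events therefore count as outcomes and use up the first event.

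The consequence is dilution towards the null and added noise in one secondary outcome of a pilot. Enrolment, compliance and the sample size are untouched.

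The size cannot be established from the article. On an assumed 2-8% of 84 it is about 2 to 7 patients, possibly fewer after the fitness screen. On the further assumed rates above, a risk ratio of about 0.71 would appear as 0.76 to 0.89. These magnitudes rest wholly on the assumptions; the direction does not. The change is worth making, but it does not threaten the trial's main conclusions.

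**What to change.** Define time to first adverse cardiovascular event from the date of randomisation in both arms, counting only events on or after that date. Report qualifying events between surgery and randomisation by arm as a baseline characteristic, so no information is lost. State the same origin for time to death, for which the article gives none; this is a clarification and not a correction.

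The origin should not be moved on to the start of CR. Induction may take place "at the induction CR meeting scheduled 4–6 weeks after aortic aneurysm repair", but events between allocation and induction occur after randomisation and belong in the comparison.

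The cost is a sentence or two in the outcome definition and slightly fewer counted events. The article does not list the case report form fields, so the sponsor should confirm that the dates of surgery, randomisation and each event are captured. Allocation is open and recruitment has begun, so the change should be recorded before events are examined by arm.

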
### Power calculation

A pilot RCT of 84 patients is planned; to estimate enrolment rates in the trial, we plan to approach 140 patients for consent. We expect that at least 60% (95% confidence interval 50.7%-68.8%) will agree to enrolment, leading to the randomised study of 84 patients. The lower margin of the 95% confidence interval for this enrolment rate (50.7%) provides adequate precision to establish that at least 50% of aortic aneurysm patients will agree to participate in an RCT of CR; establishing the feasibility of a definitive multi-centre national RCT. The study will cease recruitment when either 84 patients have been randomised or 140 patients approached. The feasibility trial is itself feasible because St George’s and Leicester perform in excess of 200 thoracic or abdominal aneurysm repairs per annum. The target enrolment is realistic because previous RCTs of A/TAA surgery in the UK have reported 74-76% enrolment rates (EVAR-1 and EVAR-2; NIHR HTA trials [18,19]).

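### The printed 95% interval of 50.7% to 68.8% is not the interval for 84 of 140, and the claim to establish at least 50% enrolment holds only if about 60% is actually observed

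*Protocol article*

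**What the plan says.** The Power calculation section of the protocol article sets the size of the pilot from the first primary outcome, the enrolment rate. It gives the denominator: "to estimate enrolment rates in the trial, we plan to approach 140 patients for consent". It gives the expected rate and its interval: "We expect that at least 60% (95% confidence interval 50.7%-68.8%) will agree to enrolment". It gives the resulting numerator: "leading to the randomised study of 84 patients".

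The next sentence repeats the lower limit of 50.7% and rests the feasibility argument on it, saying that it "provides adequate precision to establish that at least 50% of aortic aneurysm patients will agree to participate in an RCT of CR".

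Recruitment is capped in two ways: "The study will cease recruitment when either 84 patients have been randomised or 140 patients approached". The section supports the target with enrolment of 74-76% in two earlier UK trials of aneurysm repair. It names no interval method, gives no denominator other than 140, and states no probability of clearing 50%.

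**The concern.** There are two separate problems.

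First, the section fixes every input to the interval (140 approached, 60% agreeing, 84 randomised), yet the printed limits are wider than those inputs give. This is a wrong figure, not a detail left to a fuller document. It appears in two consecutive sentences, and the second uses it as the basis of the feasibility argument.

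Second, an interval drawn around an expected rate shows what would be concluded if exactly that rate were observed. It does not show how likely the trial is to observe a rate that high. To say that the design can establish at least 50% enrolment, one needs the chance that the lower limit clears 50% at plausible true rates.

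This is the article's only quantitative argument for the size of the pilot. A reader planning the definitive trial could take an observed 57% or 58%, with a lower limit below 50%, as a surprise. It is an ordinary result when the true rate is 60%.

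**Working it through.** **Inputs** (all from the Power calculation section): n = 140 approached; x = 84 randomised; 84/140 = 0.600; 95% two-sided interval, since both limits are given; threshold 50%, judged by the lower limit; stop at 84 randomised or 140 approached.

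**Step 1. Try to reproduce the printed interval, 50.7% to 68.8%.**

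- Wald: p ± 1.96 × √(p(1−p)/n) = 0.600 ± 1.96 × √(0.24/140) = 0.600 ± 1.96 × 0.0414 = 0.600 ± 0.081.
- Exact (Clopper-Pearson): lower limit = 2.5% quantile of Beta(84, 57); upper limit = 97.5% quantile of Beta(85, 56).
- The other methods use their usual formulas.

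| Method, 84/140 | Lower % | Upper % |
|---|---|---|
| Printed | 50.7 | 68.8 |
| Exact (Clopper-Pearson) | 51.4 | 68.2 |
| Wilson | 51.7 | 67.7 |
| Wilson, continuity-corrected | 51.4 | 68.1 |
| Wald | 51.9 | 68.1 |
| Wald, continuity-corrected | 51.5 | 68.5 |
| Agresti-Coull | 51.7 | 67.7 |
| Jeffreys | 51.8 | 67.8 |
| Logit | 51.7 | 67.8 |

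None matches. All eight lower limits are above 50.7% and all eight upper limits are below 68.8%.

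**Step 2. Look for a design that does match.** Denominators from 80 to 159 and rates of about 55% to 65% were searched by Wald, Wilson, exact, Agresti-Coull and Jeffreys. Two cases round to the printed limits: exact for 72/120 (50.66% to 68.83%) and Jeffreys for 66/110 (50.68% to 68.80%). Both are 60% of a smaller denominator.

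**Step 3. Find the count needed for the lower limit to exceed 50%, with 140 approached.**

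| Enrolled | Observed rate | Exact lower limit | Wilson lower limit | Wald lower limit |
|---|---|---|---|---|
| 81 | 57.9% | 49.2% | 49.6% | 49.7% |
| 82 | 58.6% | 49.95% | 50.3% | 50.4% |
| 83 | 59.3% | 50.7% | 51.0% | 51.1% |
| 84 | 60.0% | 51.4% | 51.7% | 51.9% |

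The exact method needs at least 83; Wilson and Wald need at least 82.

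**Step 4. Probability of reaching that count.** With X ~ Binomial(140, π):

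| True rate π | Exact: P(X ≥ 83) | Wilson or Wald: P(X ≥ 82) |
|---|---|---|
| 60% | 0.604 | 0.668 |
| 62.5% | 0.809 | 0.852 |
| 65% | 0.933 | 0.952 |
| 70% | 0.997 | 0.998 |
| 74% | >0.999 | >0.999 |

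**Step 5. Check the stopping rule.** If the 84th patient is randomised at or before the 140th approach, the observed rate is at least 60% and the exact lower limit is at least 51.4%, so the criterion is met. The only other way to meet it by the exact method is 83 of 140. At a true 60% these have probabilities 0.537 and 0.604 − 0.537 = 0.067, which sum to 0.604. Stopping early therefore does not change the result in Step 4.

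**The case against.** **The slip is harmless.** The correct interval is narrower than the printed one and its lower limit is higher, so the inference that the section draws from it is slightly strengthened. This stands. A reader might infer that correcting the interval overturns the feasibility argument; it does not. The figure is still wrong and should be replaced.

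**No power was promised.** The objectives are to estimate enrolment and compliance, and an expected rate with its interval is a common justification for a pilot. No assurance target is stated, so none is missed. This also stands. What remains is the claim to establish at least 50%, which goes beyond estimation and is not supported by an interval at the expected rate alone.

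**A true rate of exactly 60% is the least favourable reading.** The text expects at least 60% and cites 74-76% elsewhere; at those higher rates success is nearly certain. This is fair, and it is why the probabilities should be shown over a range. But 60% is the rate from which the article derives both the 84 and the interval, and its Background says that it is not known whether rehabilitation is feasible or acceptable in this older group.

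**Stronger readings that the document does not support.** A reader might conclude that the interval was certainly computed for 72/120. The match only suggests a leftover from another sample size: no such denominator appears, and 66/110 by Jeffreys rounds to the same limits. A reader might treat the 50% threshold as a formal go/no-go rule, but the section makes a statement about feasibility and sets no progression rule. A reader might also object that 84 randomised is not guaranteed, because the abstract says "Aneurysm-CaRe will randomise 84 patients at two sites". The two-way recruitment cap already discloses that recruitment may end with fewer.

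**Conclusion.** The concern holds in two limited parts.

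The printed interval is wrong for the stated design by 0.7 percentage points at the lower limit (50.7% against 51.4%) and 0.6 at the upper (68.8% against 68.2%), taking the exact method. The mismatch itself does not depend on the choice among the eight methods tried. The error is in the conservative direction and changes no sample size.

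The wording about establishing at least 50% enrolment is too strong at the planning rate. If the true rate is 60%, the lower limit fails to clear 50% with probability 1 − 0.60 = 0.40 by the exact method, or 1 − 0.67 = 0.33 by Wilson or Wald. By 65% the exact failure probability is about 0.07, and at 70% it is below 0.01. These figures assume independent patients with a common probability of agreeing, and a two-sided 95% interval compared with 50%.

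The passage should be corrected, but it does not make the pilot unsound.

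**What to change.** Change two sentences of the Power calculation section.

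1. Replace the interval with 51.4% to 68.2%, labelled as the exact (Clopper-Pearson) 95% interval for 84 of 140, and replace the repeated lower limit of 50.7% with 51.4%.
2. Replace the claim of adequate precision with a conditional statement and its probabilities, for example: *If 60% enrolment is observed, the lower 95% limit would exceed 50%. With recruitment continuing to 84 randomised or 140 approached, the probability that the exact lower limit exceeds 50% is 0.60, 0.93 and above 0.99 at true enrolment rates of 60%, 65% and 70%.*

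Restating the denominator as 120 is not a remedy: 60% of 120 is 72, which contradicts both the 84 randomised and the 140 approached.

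The cost is a text edit, with no extra patients and no change to recruitment. The stated assurance becomes less favourable at the 60% planning rate.
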